## Abstract

**Background::**

Type 2 diabetes is a kind of metabolic disease. Its clinical characteristic is hyperglycemia. Recently, more and more elderly people suffer from type 2 diabetes, and the glycemic variability of the elderly is greater. In addition, blood sugar variation is more likely to cause diabetes complications than simple hyperglycemia. Sancai podwer (SC) is based on the theory of traditional Chinese medicine and gradually formed in the summary of clinical experience. It has the effect of lowering blood sugar and alleviating clinical symptoms of diabetes. But the existing evidence of its efficacy on glycemic variability is insufficient. So, in our study, the randomized controlled trials will be used as a research method to explore the effects of SC on glycemic variability of type 2 diabetes.

**Method::**

We will use randomized controlled experiments based on the recommended diagnostic criteria, inclusion and exclusion criteria. A total of 60 elderly patients with type 2 diabetes will be randomly divided into treatment group and control group, 30 cases in each group. The control group will receive conventional western medicine and the intervention group will receive SC combined with western medicine. The standard deviation and coefficient of variation of blood glucose level will be used as evaluation indexes.

**Discussion::**

This study can provide evidence for the clinical efficacy and safety of SC in elderly patients with type 2 diabetes mellitus.

**Trial registration::**

This study is registered on the Chinese Clinical Trial Registry: ChiCTR2000032611.

## Introduction

1

Type 2 diabetes mellitus (T2DM) is a metabolic disease. Its clinical feature is hyperglycemia, and T2DM is also a common clinical endocrine disease and elderly chronic disease.^[1]^ With the aging of populations worldwide growth, T2DM is increasingly common in the elderly.^[2]^ T2DM occurred in 9% of the adult population, about 20% over the age of 65.^[3]^ According to the World Health Organisation, in 2019, it is estimated that diabetes over 65 years old is 111 million and will reach 276 million by 2045.^[4]^ Inevitably, this will cause further pressure on healthcare resources and medical service providers.^[5]^

Due to the course of type 2 diabetes in elderly patients is generally long and the condition is complex, the function of islet B cells is gradually exhausted, and the ability of the body to regulate blood glucose is relatively weak.^[6]^ The amplitude of blood glucose fluctuation in elderly patients increases accordingly.^[7]^ To make matters worse, unstable blood sugar is closely related to the occurrence and development of chronic complications of diabetes.^[8–11]^ Blood glucose fluctuations are significantly associated with the severity of coronary heart disease and the recurrence of acute myocardial infarction in diabetic patients.^[8,9]^ The glycemic variability is also a relevant risk factor for diabetic retinopathy.^[12]^ Long-term blood glucose fluctuation will affect the occurrence and development of chronic kidney disease.^[13–15]^

Western medicine's treatment of type 2 diabetes with oral medicine revolves around aspects such as promoting insulin secretion, improving insulin resistance, and delaying the absorption of glucose in the gastrointestinal tract. Although it can effectively lower blood sugar, the treatment target is relatively single and cannot effectively relieve oxidative stress and vascular endothelial damage. In addition, it has some side effects and adverse reactions. The common adverse reactions caused by the clinical use of hypoglycemic drugs mainly include hypoglycemic reactions, digestive tract reactions, allergies, and weight gain, severe may cause liver damage.^[16–18]^ Research data show that the incidence of adverse reactions of taking hypoglycemic drugs for type 2 diabetes is 7.6%.^[19]^

SC was founded on the basis of 3 ancient Chinese medicine prescriptions, namely ”San Cai Tang,” “Jiao Tai Wan,” and “Fructus Mume.” The reason for choosing these Chinese herbal medicines to treat diabetes is based on the theory of traditional Chinese medicine (TCM). SC can reduce blood sugar and there is a certain pharmacological research foundation (Table 1). Moreover, our team has conducted a single-blind randomized controlled trial and confirmed that SC can effectively improve endothelial dysfunction (ED), insulin resistance (IR), hyperinsulinemia, and mild vascular dementia (VaD) symptoms.^[20]^ The mechanism of IR is very complicated. So far, many basic researches and clinical trials have proved that IR is associated with inflammation, oxidative stress (OS), and abnormal signal pathways in cells.^[21]^ In addition, oxidative stress will aggravate the damage of islet function.^[22]^ Under the combined effect of the above mechanisms, the variability of blood glucose will also increase. The elderly are more susceptible to various unfavorable factors due to their long course of illness and complicated condition, leading to unstable blood glucose. Therefore, the emphasis of this study is to observe the safety and clinical effect of SC and Western Medicine on T2DM. We hope that through this study, we can find more evidence-based medical evidence that SC reduces blood glucose variability, and provide patients with more treatment methods.

**Table 1 T1:**
[figure not shown]
The action of each Traditional Chinese medicinal herb.

## Methods/Design

2

### Hypotheses

2.1

SC could reduce blood glucose variability in elderly patients with type 2 diabetes and relieve clinical symptoms.

### Objectives

2.2

1.To compare the difference in blood glucose variability between the intervention group and the control group through standard deviation of blood glucose level (SDBG) and coefficient of variation (CV).2.To compare the difference in the improvement of diabetes symptoms between the intervention group and the control group.3.To analyze the synergy or other effects of SC on type 2 diabetes.

### Study design and settings

2.3

The study will be a double-blind, randomized controlled trial. It will be carried out in the Hospital of Chengdu University of Traditional Chinese Medicine. The study protocol follows the recommendations of the Standard Protocol Items for Randomized Trials and the Consolidated Standards of Reporting Trials Extension for CHM Formulas statemen.^[23,24]^ The author of this protocol will truthfully inform the participants of this experimental study, procedures, potential risks, and benefits. With their consent, they will sign an informed consent form and abid by the schedule represented in Fig. 1. It is worth mentioning that participants can only participate in the study if they have fully read, agreed, and signed an informed consent form.

**Figure 1 F1:**
[figure not shown]
Flowchart of the trial. Figure shows the flowchart of the study process.

### Participants

2.4

Participants will be composed of outpatients and inpatients of the Hospital of Chengdu University of Traditional Chinese Medicine. T2DM diagnosis based on World Health Organization (1999) criteria.^[25]^

#### Western medicine diagnostic criteria

2.4.1

(1)Islet cell antibody (ICA), glutamate decarboxylase antibody (GADA) are negative.(2)Typical diabetes symptoms and random venous PG ≥ 11.1 mmol/L or FPG ≥ 7.0 mmol/L or in an oral glucose tolerance test, 2hPG ≥ 11.1 mmol/L, or have been diagnosed as diabetes in the past.

#### TCM diagnostic criteria

2.4.2

Based on the relevant standards in “Guiding Principles of Clinical Research on New Drugs of Traditional Chinese Medicine (2002)” and “Guidelines for Prevention and Treatment of Diabetes TCM (2007),” the dialectical standards for the syndrome of yin deficiency and heat in this study were formulated. The symptoms can be seen: dry mouth and throat, polydipsia and polyuria, polyphagia, irritability, red face, night sweats, red tongue or crimson tongue, thin white tongue coating or thin yellow tongue coating or less tongue coating, thready and rapid pulse or taut and rapid pulse.

#### Inclusion criteria

2.4.3

The research will be carried out in China. Patients will be enlisted from the Hospital of Chengdu University of Traditional Chinese Medicine. We will recruit participants according to the following inclusion criteria

(1)Participants are 65 to 85 years old.(2)Meet the diagnostic criteria for type 2 diabetes.(3)The BMI is between 18 and 28 kg/m^2^.(4)Blood biochemical indicators such as liver and kidney function are normal.(5)Accept and sign the informed consent.

#### Exclusion criteria

2.4.4

Patients will be excluded if they meet the following criteria:

(1)Glycated hemoglobin is >10%.(2)Diabetes is in the period of acute complications, such as diabetic ketoacidosis, diabetic hyperosmolar nonketotic coma, hypoglycemic coma, or severe unconscious hypoglycemia.(3)Diabetic patients with severe chronic complications, such as diabetic foot with infection, diabetic nephropathy with renal insufficiency, diabetic retinopathy of >3 stages, etc.(4)Patients with anxiety, depression, mania, or other mental illness.(5)Patients with a history of stroke, transient ischemic attack, unstable angina, and myocardial infarction in the first 6 months of the study were patients with congestive heart failure.(6)A history of acute or chronic pancreatitis.(7)Allergic to Chinese herbal medicine.(8)The history of the use of immunosuppressants and glucocorticoids in the past 3 months.(9)Involuntary ability and other diseases affecting glucose metabolism.(10)Patients who were enrolled in other clinical tests in the past 3 months.

### Sample size calculation

2.5

The study used SBDG and CV as the main outcome indicators. In the preliminary experiment, the mean value of SBDG between the 2 groups was 0.39, and the standard deviations of treatment group and control group were 0.28 and 0.35 respectively. On the other hand, the mean value of CV between the 2 groups was 0.41, and the standard deviations of treatment group and control group were 0.31 and 0.67 respectively. Set *α* to 0.05 and *β* to 0.1. The sample sizes calculated using PASS 11 software were 14 and 25, respectively. In order to ensure statistically meaningful results, considering the 20% dropout rate, and according to the formula of n ^ = n/(1–f), the total number of studies was determined to be 60 cases, 30 cases per group.

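### The sample size of 25 per group for CV, which lies behind 30 per group, does not follow from its printed inputs: they give 35, and about 75% rather than 90% power with 24 completers.

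*Protocol article*

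**What the plan says.** Section 2.5 (Sample size calculation) names SDBG and CV as the main outcomes, as does section 4.1, and takes planning values from a preliminary experiment.

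- SDBG: "the mean value of SBDG between the 2 groups was 0.39"; the SDs given are 0.28 (treatment) and 0.35 (control).
- CV: "the mean value of CV between the 2 groups was 0.41"; the SDs given are 0.31 (treatment) and 0.67 (control).
- Error rates: "Set *α* to 0.05 and *β* to 0.1". Whether the test is one- or two-sided is not stated.
- Result: "The sample sizes calculated using PASS 11 software were 14 and 25, respectively".

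The section then allows for 20% dropout with the formula n/(1–f) and arrives at 60 patients, 30 per group. No unit is printed for any pilot figure, and no pilot mean glucose is given. The formulas for SDBG and CV are in Table 2, whose content is not available here.

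**The concern.** CV has the larger of the two sample sizes, so it determines the size of the trial. Two features of its line look wrong.

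First, the control SD of 0.67 is large against a difference of 0.41, and an n of 25 looks too small for 90% power.

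Second, each patient's CV is that patient's SDBG divided by mean glucose. The two sets of pilot figures should therefore be linked through a credible mean glucose, yet they are almost equal in size.

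At stake is whether the stated 90% power holds for CV, and whether a reader can tell what CV effect the trial was sized to detect.

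**Working it through.** **Inputs (section 2.5).** SDBG difference 0.39, SDs 0.28 and 0.35. CV difference 0.41, SDs 0.31 and 0.67. Alpha 0.05, taken as two-sided. Power 0.90. Dropout 20%. The wording about a mean value between the groups is read as the difference between them, since only that reading works in the formula.

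**Formula.** Per group, n = (z₁₋α/₂ + z₁₋β)² × (s₁² + s₂²) / d², with (1.960 + 1.282)² ≈ 10.507.

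**Step 1: SDBG.** 10.507 × (0.0784 + 0.1225) / 0.1521 = 13.88, so 14. This is the stated figure. It shows that the formula is the one intended and that 14 and 25 are per-group numbers.

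**Step 2: CV.** 10.507 × (0.0961 + 0.4489) / 0.1681 = 34.07, so 35, not 25.

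Other settings do not yield 25 either:

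| Setting for CV | n per group |
|---|---|
| Two-sided, 90% power, t-based | 36 |
| One-sided, 90% power | 28 |
| Two-sided, 80% power (contradicts the stated β) | 26 |
| One-sided, 80% power (contradicts the stated β) | 21 |
| Two-sided, 90%, one SD for both arms: 0.31 / average 0.49 / 0.67 | 13 / 31 / 57 |

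Solving backwards, 25 at two-sided 90% power needs, for example, a control SD of about 0.55 or a difference of about 0.48.

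**Step 3: dropout.** The printed formula gives 25 / (1 – 0.2) = 31.25, so 32 per group. The figure of 30 equals 25 × 1.2, which is a different rule. Conversely, 30 × 0.8 = 24 completers, below the stated 25. With 35 the formula gives 35 / 0.8 = 43.75, so 44 per group.

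**Step 4: power for CV with 24 completers per arm (noncentral t, unequal variances, two-sided).**

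- Printed inputs (0.41; 0.31, 0.67): 0.752. The normal approximation gives 0.777.
- Control SD 0.55 instead of 0.67: 0.872.

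With all 30 per arm retained, the printed inputs give 0.844.

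**Step 5: do the SDBG and CV lines fit together?** Mean glucose is not given, so 6 to 14 mmol/L is assumed. For orientation, the diagnostic limits in section 2.4.1 are 7.0 and 11.1 mmol/L. SDBG is taken to be in mmol/L. Dividing the SDBG figures by a common mean glucose gives:

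| | Expected CV, fraction | Expected CV, percentage points | Printed |
|---|---|---|---|
| Difference | 0.028–0.065 | 2.8–6.5 | 0.41 |
| SD, treatment | 0.020–0.047 | 2.0–4.7 | 0.31 |
| SD, control | 0.025–0.058 | 2.5–5.8 | 0.67 |

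Read as fractions, the printed figures are roughly 6 to 27 times too large. Read as percentages, the two SDs are roughly 4 to 15 times too small.

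A second check on the percentage reading does not rest on that division. In simulated 7-point profiles with an assumed mean of 9 and within-day SD of 1 mmol/L, sampling error alone gives SDBG an SD of 0.28, the printed treatment value. The same profiles give CV an SD of about 3.2 points, against the printed 0.31.

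**The case against.** The strongest objection is to the scale argument. CV equals SDBG over mean glucose within a patient. The ratio of the two SDs equals mean glucose only if all patients share one mean, and the ratio of the two differences only if both arms do. With assumed values, SDBG 2.0 at mean glucose 9.0 against SDBG 1.61 at 7.4 gives an SDBG difference of 0.39 and a CV difference of about 0.47 percentage points. So 0.41 read as a percentage is attainable on its own. A common tenfold slip would also fit the CV difference and the treatment SD (mean glucose 9.0 to 9.5). The control SD might then be explained by a wider spread of mean glucose in that arm. A slip common to all three CV figures would leave n unchanged.

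This stands as a limit on what the mismatch proves. A reader might infer that the CV figures are impossible in either unit, and that 30 per group therefore rests on wrong CV inputs. The document does not support that. It prints no unit and no pilot mean glucose, and the mismatch does not show whether the SDBG or the CV line is at fault. Nor is 25 the output of the printed CV inputs, so neither is 30.

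The objection does not touch steps 2 to 4. The ratio of difference to SDs is free of units, so a common rescaling of the CV line still gives 35.

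**Conclusion.** The stated 25 for CV is not reproducible from the printed inputs. They give 35 per group at two-sided alpha 0.05 and 90% power, and 28 even if one-sided. The dropout step contradicts its own formula (32, not 30). If the printed CV inputs are right, the planned 30 per group delivers about 75% power for CV with 24 completers, not 90%. These results use only figures in section 2.5, apart from the sidedness.

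The poor fit between the SDBG and CV lines is a further sign of a misprint. It rests on the assumed 6 to 14 mmol/L and mainly on the SDs.

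It would go too far to conclude that the trial is underpowered. Either line may be misprinted. If CV were SDBG divided by a common mean glucose, CV would need only 14 per group. What is established is that the stated power for CV is unsupported as printed.

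**What to change.** In section 2.5:

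1. Check the pilot SDBG and CV differences and SDs against their source, state the unit of each, and correct whichever are wrong.
2. State the sidedness, rerun the CV calculation and apply the printed dropout formula to the result.
3. Restate the n for CV and the power that 30 per group (24 completers) delivers. If the printed CV figures stand, give about 75% power instead of 90%.

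This costs a look at the pilot source, a short rerun and a corrected paragraph. It requires no increase in enrolment; the price may be a less favourable stated power for one of the two primary outcomes.

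### Section 2.5: the CV sample size of 25 per group does not follow from the printed inputs; the formula that returns the stated 14 for SDBG gives 35 for CV

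*Protocol article*

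**What the plan says.** All the figures are in section 2.5 (Sample size calculation) of the protocol article.

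- Outcomes sized: "The study used SBDG and CV as the main outcome indicators". The first is SDBG, with two letters transposed. Section 4.1 names the same two as primary.
- SDBG effect, from a preliminary experiment: "the mean value of SBDG between the 2 groups was 0.39". The SDs printed for it are 0.28 under treatment and 0.35 under control.
- CV effect, from the same source: "the mean value of CV between the 2 groups was 0.41". The SDs printed for it are 0.31 under treatment and 0.67 under control.
- Error rates, given once for both outcomes: "Set *α* to 0.05 and *β* to 0.1".
- Results of the calculation, SDBG first and CV second: "The sample sizes calculated using PASS 11 software were 14 and 25, respectively".

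The section then allows for 20% dropout and settles on 30 per group, 60 in total. It does not say whether the test is one- or two-sided. Section 4.5 plans an independent-samples t test, or a Mann–Whitney test for non-normal data, with significance at P below .05. It mentions no one-sided test.

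**The concern.** The two outcomes have almost the same assumed effect (0.39 and 0.41), but the CV standard deviations are much less favourable. The sum of squared SDs is 0.545 for CV against 0.2009 for SDBG, a ratio of 2.71. The squared effects differ by a factor of only 1.11 (0.1681/0.1521). At the same α and β the CV sample size should therefore be about 2.71/1.11 = 2.45 times the SDBG one. The printed ratio is 25/14 = 1.79. The ratio does not depend on α, β or sidedness, provided they are the same for both outcomes.

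CV is one of the two main outcomes, and its figure is the larger, so it is the one behind the total of 60. If the inputs are right and 25 is too small, the protocol claims a 10% false-negative risk for CV that the trial does not deliver, and a null CV result would be read as more conclusive than it is.

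**Working it through.** **Formula.** For two equal groups with SDs s₁ and s₂ and difference d:

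n per group = (z₁₋α/₂ + z₁₋β)² × (s₁² + s₂²) / d²

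With two-sided α 0.05 and β 0.1, the multiplier is (1.960 + 1.2816)² = 10.507.

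**Step 1: reproduce the SDBG figure.** s₁² + s₂² = 0.0784 + 0.1225 = 0.2009; d² = 0.39² = 0.1521.

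n = 10.507 × 0.2009 / 0.1521 = 13.88, so 14, as stated. This supports three readings that the text leaves open: 0.39 and 0.41 are differences in means, α is two-sided, and 14 and 25 are per-group numbers.

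**Step 2: the same formula for CV.** s₁² + s₂² = 0.0961 + 0.4489 = 0.5450; d² = 0.41² = 0.1681.

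n = 10.507 × 0.5450 / 0.1681 = 34.07, so 35. The stated figure is 25. With the t distribution (equal-variance or Welch) CV needs 36 and SDBG 15. Since 14 matches the normal approximation, 35 is the like-for-like comparison.

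**Step 3: does another setting return both 14 and 25?**

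| Setting | SDBG | CV |
|---|---|---|
| Stated in the protocol | 14 | 25 |
| Two-sided, 90% power | 13.88 → 14 | 34.07 → 35 |
| Two-sided, 90%, simple average of the SDs | 14 | 31 |
| Two-sided, 80% power | 10.37 → 11 | 25.45 → 26 |
| One-sided, 90% power | 11.31 → 12 | 27.77 → 28 |
| One-sided, 90%, simple average of the SDs | 12 | 24.46 → 25 |

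None returns both. Using only the larger or only the smaller SD, or inflating for the Mann–Whitney test, does not either.

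**Step 4: power for CV if the printed inputs stand (two-sided 0.05).** Twenty per cent dropout from 30 leaves 30 × 0.8 = 24 per group. By normal approximation:

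- 24 per group: Φ(0.41/√(0.545/24) − 1.96) = Φ(2.721 − 1.960) = 77.7%
- 30 per group: Φ(0.41/√(0.545/30) − 1.96) = Φ(3.042 − 1.960) = 86.0%

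| Evaluable per group | Normal | t test | Welch |
|---|---|---|---|
| 24 | 77.7% | 75.9% | 75.2% |
| 25 | 79.3% | 77.7% | 77.0% |
| 30 | 86.0% | 84.9% | 84.4% |

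SDBG power with 24 per group is 98.9% (normal) or 98.6–98.7% (Welch and t test).

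**The case against.** The strongest reply is that the document shows a disagreement between inputs and result but not its cause. It is tempting to infer that the CV calculation was run on different settings, for instance at 80% power. The documents do not support that: 80% power gives 26 for CV rather than 25, and 11 for SDBG rather than 14. A misprinted input would explain the gap equally well. On the two-sided, 90% setting that yields 14 for SDBG, a CV difference of 0.48 gives 10.507 × 0.545/0.2304 = 24.85, so 25. A control SD of 0.55 gives 10.507 × (0.0961 + 0.3025)/0.1681 = 24.9, also 25. Neither value is in the protocol; they only show how small a slip would be enough. This part of the reply stands, and 35 should not be written in before the source is checked.

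Second, sidedness is not stated. Under a one-sided 0.05 test, CV power by normal approximation would be about 86% with 24 per group and 92% with 30, so the statement that 90% is missed even without dropout needs the two-sided reading. That reading is the better supported, through the match at 14 and the plain significance rule in section 4.5, but it remains an assumption. The one-sided reading does not rescue 25 either: with the SDs kept separate it gives 28.

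Third, a reader might infer that the justification should rest on SDBG alone, since that outcome is well powered. The arithmetic does not require it, and the protocol names both outcomes as primary.

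**Conclusion.** The point holds as an inconsistency within section 2.5. From the printed inputs, CV needs 35 per group (36 by t test) for β 0.1, against the stated 25. That is a shortfall of 10 per group, too large for rounding or for the choice between normal and t distributions to explain. Either a CV input or the figure 25 is wrong.

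The consequence for power is conditional. It would go too far to say flatly that the trial has about three-quarters power for CV. That figure requires that the printed inputs are right, that 0.41 is the difference in means, that the test is two-sided and that 24 per group are evaluable. On those conditions the false-negative risk for CV is about 22–25% instead of 10%; with no dropout it is about 14–16%. SDBG is not affected.

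This does not depend on an unseen analysis plan or fuller protocol, because the inputs and the result that disagree are printed in the same paragraph. It should be corrected, since the stated power concerns a main outcome.

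**What to change.** 1. Check the CV difference and both CV standard deviations against the pilot data and the PASS output, and correct whichever of the inputs or the figure 25 is wrong.
2. If the printed inputs stand, replace 25 with 35–36 evaluable per group as the requirement for β 0.1. Keep the total at 60, and state the CV power as about 75–78% with 24 evaluable per group (about 84–86% with no dropout) instead of 90%. The SDBG power can be given as about 99% with 24 per group.
3. If an input was misprinted, print the right value and confirm that it returns 25 on the settings that give 14 for SDBG.
4. In either case, state that the test is two-sided and that 0.39 and 0.41 are differences in means.

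The cost is one reworded paragraph and, if the inputs stand, a less favourable stated power for CV. No extra patients are needed.

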### Statistical analysis

4.5

Data processing uses SPSS statistical software version 17.0 (IBM Corporation). Normally distributed variables are expressed as mean and standard deviation; non-normally distributed variables are expressed as median and quartile range. Normally distributed variables between groups using independent sample *t* test, rather than the normal difference variables using Mann–Whitney *U* test. In the comparison group, paired *t* test variables were normally distributed, non-normally distributed variables the Wilcoxon rank sum test. *P* < .05 was considered a statistically significant difference. Study figures were created using SigmaPlot (Systat Software Inc.).

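### The stated 60 patients do not follow from the protocol's own dropout formula: 25 per group at 20% dropout gives 32 per group (64), and 30 per group leaves 24 evaluable

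*Protocol article*

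**What the plan says.** Section 2.5 (Sample size calculation) names SDBG and CV as the main outcomes. The error rates are given as "Set *α* to 0.05 and *β* to 0.1". For SDBG, "the mean value of SBDG between the 2 groups was 0.39"; its two standard deviations are 0.28 (treatment) and 0.35 (control). For CV, "the mean value of CV between the 2 groups was 0.41", with standard deviations of 0.31 (treatment) and 0.67 (control). The software output is reported as 14 for SDBG and 25 for CV, without saying whether these are per group or in total.

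The section then inflates for loss, "considering the 20% dropout rate", cites the formula n/(1 − f), and ends: "the total number of studies was determined to be 60 cases, 30 cases per group". The Method paragraph of the abstract carries the same size: "A total of 60 elderly patients with type 2 diabetes will be randomly divided into treatment group and control group, 30 cases in each group".

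**The concern.** Every input to the last step is printed, and so is the formula, but the printed result is not what the formula gives. The larger of the two calculated sizes is 25. Dividing it by 0.80 gives more than 30.

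What is at stake is whether the plan provides the allowance it claims. If 20% of patients are lost, as planned for, fewer patients remain per group than the section says are needed. Section 4.4 gives several routes out of the trial (withdrawal by the participant, inability to continue treatment, not following the plan, joining another trial), so the allowance is not a formality. A sample-size statement is also one that readers recompute, and this one fails on a simple division.

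**Working it through.** **Inputs (all from section 2.5).** Calculated sizes 14 (SDBG) and 25 (CV); dropout f = 0.20; formula n/(1 − f); stated result 30 per group, 60 in total.

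**Are 14 and 25 per group?** The section does not say. Take 0.39 as the between-group difference, a two-sided α of 0.05 and 90% power. Then n per group = (s₁² + s₂²)(1.96 + 1.2816)²/d².

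- SDBG: (0.28² + 0.35²) × 10.507/0.39² = 0.2009 × 10.507/0.1521 = 13.88, so 14.

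The stated 14 is therefore reproduced as a per-group size. That supports reading the companion 25 as per group too.

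**Dropout step with the plan's formula.** 25/(1 − 0.20) = 31.25, so 32 per group and 64 in total.

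**Other readings with the same formula.**

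| Reading | Calculation | Total |
|---|---|---|
| 25 per group, rounded down | 31.25 → 31 | 62 |
| Two-group total of 50 | 50/0.80 = 62.5 | 63, or 64 with equal groups |
| 25 as a total | 25/0.80 = 31.25 | 32 |
| 14 per group | 14/0.80 = 17.5 → 18 | 36 |

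None gives 60. The stated figure appears only as 25 × (1 + 0.20) = 30, which is n(1 + f).

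**What 30 per group provides.**

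- Evaluable at 20% dropout: 30 × 0.80 = 24, one below 25.
- Largest dropout that still leaves 25: 1 − 25/30 = 16.7%.

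**Effect on power.** Same assumptions as above, with 0.41 as the CV difference. Normal approximation: power = Φ(d/√((s₁² + s₂²)/n) − 1.96). For CV, s₁² + s₂² = 0.31² + 0.67² = 0.545.

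- CV, n = 24: 0.41/√(0.545/24) = 2.721; Φ(0.761) = 77.7%.
- CV, n = 25: 0.41/√(0.545/25) = 2.777; Φ(0.817) = 79.3%.
- SDBG, n = 24: 0.39/√(0.2009/24) = 4.263; Φ(2.303) = 98.9%.

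The unequal-variance t test gives 75.2%, 77.0% and 98.6% respectively. Going from 25 to 24 evaluable thus costs 1.6 to 1.8 points for CV. SDBG is not affected in practice, since 24 is well above 14.

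**The case against.** The strongest reply is that this hardly matters. The loss is one evaluable patient per group, SDBG has ample power either way, and CV power moves by less than 2 points. That is right, and it limits the weight of the point. It does not make the printed figure follow from the printed formula.

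A second reply is that the section never labels 25 as per group, and 60 would be more than enough if 25 were a total. The per-group reading is indeed inferred. But 14 is reproduced as a per-group size, and treating 25 as a total does not lead to 60 either.

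A third is that patients who drop out might still be analysed. Section 2.6 mentions such an analysis only for unblinded participants, and section 2.5 itself treats dropouts as patients to be replaced by inflation.

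Two stronger readings are tempting. One is that the dropout slip is why the trial falls short of 90% power for CV, so that 64 patients would repair it. The figures do not support this: 32 per group at 20% dropout leaves 25.6, that is 25 or 26 evaluable, with roughly 77–81% power on the same assumptions. Even with no dropout, 32 per group gives 87–88%. The other is that the documents fix a correct requirement of 35 per group for CV, and so 44 per group after inflation. They do not. Section 2.5 does not state sidedness, and its wording leaves room for doubt whether 0.41 is a between-group difference. Two-sided at 90% power, the CV inputs give 35 to 36 per group; one-sided, 28 to 29. That question concerns the 25 itself and is separate from the dropout step.

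**Conclusion.** The point holds as an arithmetic error in a stated sample-size figure. With the plan's own 25, 20% and n/(1 − f), the size is 32 per group and 64 in total, so the stated 30 and 60 are short by 2 per group and 4 overall. In evaluable patients at the planned dropout the shortfall is one per group, 24 against 25, and the true allowance around 25 is 16.7%.

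The division needs no assumption about sidedness or effect size; it rests only on reading 25 as per group. The power figures rest in addition on a two-sided test at 0.05 and on 0.39 and 0.41 being between-group differences. On that footing the slip accounts for under 2 points of CV power. The rest of the gap between 75–78% and the planned 90% comes from a base figure of 25 that the stated CV inputs do not support.

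**What to change.** Keep 60 patients and correct the sentence in section 2.5. State that 30 per group leaves 24 evaluable at 20% dropout, or that the allowance is 16.7% around 25 evaluable. Say that 14 and 25 are per group, if they are. Restate power for each primary outcome at 24 per group, with sidedness and the meaning of 0.39 and 0.41 made explicit. Under the assumptions above, that is about 99% for SDBG and about 75–78% for CV.

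This costs a few lines of text and no patients, but the restated CV power will be visibly below 90%, and the text should not present the difference as a result of dropout. If the sponsor prefers to keep the 20% allowance around 25, the size becomes 32 per group (64), four more patients. In that case the text should not claim 90% power for CV unless the 25 has first been resolved.
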